### Guiding framework

We used the RE-AIM framework to guide the evaluation plan, including the selection of mixed methods [25]. This framework has been developed specifically to address questions of implementation, effectiveness, and external validity in studies conducted in real-world settings. The dimensions of the framework include: Reach (how willing the targeted population is to participate in the intervention), Effectiveness (the impact of the intervention on outcomes), Adoption (whether the intervention can be adopted with ease and minimal modifications), Implementation (what are the special issues and barriers to implementation), and Maintenance (can the intervention be maintained and will the impact continue).

To assess Reach, we will compare patient characteristics (eg, age) between those who agreed to participate in OB Nest and those who declined participation. This will allow us to measure participation and representativeness of the trial. We will also record the reasons that decliners gave to the study coordinator, and for ineligible patients we will track reasons for ineligibility. We will use a number of patient-reported outcome measures and clinical or practice-level outcome measures to assess Effectiveness on study outcomes including satisfaction, quality of care, stress, safety and utilization. To assess Adoption, we aim to understand the extent to which patients use OB Nest components, as well as the organizational or individual barriers and facilitators to provider and staff participation in OB Nest, including values and preferences. We anticipate that patients will vary in adoption of the various OB Nest components as the care model is meant to be patient-driven. To assess Implementation, we will seek to determine whether the intervention has been implemented as planned, and potential issues that need immediate adaptation before full implementation post-study would be possible. Considering the length of the study, we will not be able to fully assess Maintenance, but data on effectiveness and implementation should provide preliminary insights as to whether we can maintain this intervention post-study. Table 1 outlines the outcomes and quantitative and qualitative data collection methods, as described below, using the RE-AIM framework. This approach is well suited for the evaluation of complex, multi-component interventions like OB Nest where the aim is to evaluate not only overall program effectiveness but the potential for successful translation and sustainability.

**Table 1 Tab1:** Data collection method and outcome by RE-AIM criteria

RE-AIM criteria	Outcome	Method	Type of data
Reach	Participant and decliner characteristics, decliner reasons, and ineligibility reasons	Administrative data	QUAN
Effectiveness	Utilization (eg, in-office visits)	Administrative data	QUAN
	Maternal/fetal outcomes (eg, gestational age at delivery)	Administrative data	QUAN
	Receipt of standard prenatal testing and care (ACOG)	Administrative data	QUAN
	Patient stress	Questionnaires	QUAN
	Patient satisfaction and perceived quality of care	Questionnaires	QUAN
		Patient interviews and focus groups	qual
Adoption	Extent to which participants use intervention components	Patient interviews and focus groups	qual
		Provider and staff interviews and focus groups	qual
		Administrative data	QUAN
	Organizational or individual barriers to intervention use	Provider and staff interviews and focus groups	qual
		Patient interviews and focus groups	qual
		Document review	qual
Implementation	Implementation as planned, and issues in implementation	Patient interviews and focus groups	qual
		Provider and staff interviews and focus groups	qual
		Document review	qual
Maintenance^a^			

Abbr: QUAN = quantitative, qual = qualitative, ACOG = American College of Obstetricians and Gynecologists

^a^Effectiveness data and implementation data will inform maintenance, but maintenance will not be fully assessed due to the study length

### Setting

This study will recruit individuals from the Obstetrics Division at Mayo Clinic (Rochester, MN), a tertiary Midwest teaching hospital with a delivery rate of 2400 women annually. The practice consists of 14 full-time obstetricians, 5 maternal fetal medicine specialists, 10 certified nurse midwives (CNM), and 10 family medicine physicians. A 20 bedded level 3 neonatal intensive care unit serves as a regional referral center and is staffed by 4 full-time neonatologists. The usual model of prenatal care includes a set schedule of 12 pre-planned in-office visits with a physician or a certified nurse midwife (sometimes referred to as “providers” in this article). CNMs in this practice are registered nurses with Master of Science degrees in midwifery, and they provide a full range of prenatal care and labor and delivery services. Registered nurses in the department assist with patient care and provide patient education during provider office visits and in patient education courses. They also provide support to patients by telephone.

### Sample size

On average 2400 pregnant women receive prenatal care from the Obstetrics Division in a 12-month period, and about 60 % of these are considered to be low-risk pregnancies. We will enroll 300 patients in this study (150 patients per arm). This accounts for a withdraw/post-randomization exclusion rate as high as 10 %, so the effective sample size can be as low as 135 patients/arm. Sample size calculations are displayed in Table 2.

**Table 2 Tab2:** Sample size calculations

Outcome	Estimated rate for standard of care^a^	Improvement to be tested/expected	Power
Patient-reported outcomes			
Satisfaction with care	108.4 (SD 14.4)	115.6	98 %
Perceptions of quality of care	83.9 (SD 22.8)	91.9	86 %
Prenatal stress	12.9 (SD 7.1)	16.5	98 %
Maternal/fetal outcomes and standards of care			
Low birth weight	11 %	6 %	24 %
Gestational age at delivery	38.9 (SD 2.5)	40.2	99 %
Standard of prenatal care (measured as receiving at least 20 out of 24 items from the ACOG standards of prenatal care list)	90 %	95 %	30 %
Health care utilization			
Number of antenatal visits	14.7 (SD 4.2)	12	99 %

Abbr: ACOG = American Congress of Obstetricians and Gynecologists

^a^All calculations 2-sided with alpha of 0.05. Continuous outcomes compared to a half of standard deviation increase

We will interview up to 40 patients and conduct approximately 4 patient focus groups of 10–12 participants each. We will also interview physicians (*n* = 6) and conduct focus groups with midwives (*n* = 9), nurses (*n* = 7), and desk staff/clinical assistants (*n* = 10) at three points in time. This sample size is within standards for qualitative research, but we will increase the sample size if needed to achieve saturation in identifying themes.

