### Data collection

#### Quantitative (QUAN)

Patient characteristics will be collected for patients in both arms (*n* = 300) at time of enrollment through self-report and medical record review including: age, race/ethnicity, education level, marital status, body mass index (BMI), due date, parity, previous miscarriage, previous C-section, and insurance. The following patient-reported outcome instruments, administered by email or by mail if requested, will be used to provide data on locus of control (collected as a measure of participant characteristics at baseline), satisfaction with care, quality of care, and stress related to pregnancy in both arms:The validated Fetal Health Locus of Control Scale will be used at the time of enrollment to assess patients’ feelings of control in their pregnancies [27]. The scale contains 18 items, with 6 questions per subscale that address internal control, control by health professionals and control by God/fate/chance. Points will be summed and reported on each subscale.Patient satisfaction (primary outcome) with care will be assessed using the validated 16-item Satisfaction subscale, which is scored on a 5-point scale from ‘very dissatisfied’ to ‘very satisfied.’ The scale will be collected at the 36-week assessment [28]. Responses will be summed and converted to a 0–100 point scale where higher scores are indicative of a higher degree of satisfaction.Patient perceptions of quality of care will be assessed using the validated Prenatal Interpersonal Processes of Care (PIPC) scale [29]. The 30 items cover 3 subscales that address communication, decision making and interpersonal style. The scale will be collected at the 36 week assessment. Responses will be converted to a 0–100 scale for each subscale.Stress will be evaluated using the validated PreNatal Maternal Stress (PNMS) scale [30]. The 9-item scale will be emailed to patients at approximately 14 weeks gestation and again with additional items at approximately 24 weeks and 26 weeks gestation. Scores will be summed and averaged where higher scores are indicative of a higher degree of stress.

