### Analysis plan

#### Quantitative (QUAN)

Quantitative analysis will be performed according to the intention to treat principle, including all participants in the arm to which they were randomized, regardless of whether they received the intervention assigned or crossed over to the other treatment arm. Baseline characteristics will be reported in the study results with continuous values being reported as means and standard deviations and categorical values reported as counts and frequencies and compared between study arms using t-tests and chi-squared tests, respectively.

We will use standard techniques appropriate for participant level randomized trials, with each outcome compared between study arms using t-tests for continuous outcomes and chi-square tests for dichotomous outcomes. Any baseline imbalances (*p* < 0.05) will be explored as a possible factor to adjust for when the outcome measures are analyzed. We will use predetermined criteria for missing data when calculating scores on patient-reported surveys. The comparison of outcomes will be considered significantly different between arms at a *P* < 0.05.

Participants who move into a high risk category after 12 weeks will stay on study and be evaluated in the arm to which they were randomized. If more than 10 % of patients choose to crossover from intervention to control, a sensitivity analysis will be conducted. Trial enrollment, completeness of data collection, and fidelity of follow-up procedures will be reviewed and reported during study team meetings which will be conducted on a monthly basis. Analysis of quantitative data will be performed at the close of the study.

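### The 135-per-arm floor is not assured for the 36-week e-mailed surveys, and the 86 % power for perceived quality of care holds only at 150 per arm

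*Protocol article*

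**What the plan says.** Protocol article, Sample size: "We will enroll 300 patients in this study (150 patients per arm"). The loss allowance follows: "This accounts for a withdraw/post-randomization exclusion rate as high as 10" %, "so the effective sample size can be as low as 135 patients/arm". Table 2 gives 98 % power for satisfaction (108.4 against 115.6, SD 14.4) and 86 % for perceived quality of care (83.9 against 91.9, SD 22.8). Its footnote reads "All calculations 2-sided with alpha of 0.05".

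Protocol article, Data collection, Quantitative (QUAN): the patient-reported instruments are "administered by email or by mail if requested". For satisfaction, "The scale will be collected at the 36-week assessment", and the perceived-quality scale has the same time point. The stress scale is also e-mailed, but earlier: "emailed to patients at approximately 14 weeks gestation and again with additional items at approximately 24 weeks and 26 weeks gestation".

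Protocol article, Analysis plan, Quantitative (QUAN): all women are analysed in the arm to which they were randomized. On missing data it says "We will use predetermined criteria for missing data when calculating scores on patient-reported surveys". That concerns how a score is calculated. The article gives no expected rate of survey return.

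**The concern.** The allowance names two kinds of loss: withdrawal, and exclusion after randomization. Under Participant recruitment and randomization, the latter means women judged high-risk at about 12 weeks. Recruitment is at about 8 weeks and the two surveys fall at 36 weeks. On its face, a woman who stays in the trial but does not return the survey is counted in the 135 and has no score. The same may apply to a woman whose pregnancy ends before 36 weeks. The number analysed for these outcomes can therefore fall below the stated minimum.

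Perceived quality is part of the first research question under Study purpose. Limitations and strengths names several underpowered outcomes, and perceived quality is not among them. A reader would take a null result on it as coming from a comparison with 86 % power. If the real figure is nearer 75 %, that result would be over-read.

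**Working it through.** **Inputs.** From Sample size and Table 2: 150 per arm, 10 % allowance, two-sided alpha 0.05. Satisfaction difference 115.6 − 108.4 = 7.2, SD 14.4, standardized 0.50. Perceived-quality difference 91.9 − 83.9 = 8.0, SD 22.8, standardized 0.351. The article gives no further survey loss, so that is an assumption throughout.

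**Formula.** Power ≈ Φ(δ/SD × √(n/2) − 1.96), with n per arm. The percentages below come from the exact two-sample t-test (noncentral t) unless marked as the approximation; the two agree within about half a point.

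**Step 1: the plan's own figures.** 150 × (1 − 0.10) = 135, as stated.
- Satisfaction at 135: 0.50 × √67.5 − 1.96 = 2.15, approximation 98.4 % (t-test 98.4 %). The stated 98 % reproduces. At 150 it would be 99.1 %.
- Perceived quality at 135: 0.351 × √67.5 − 1.96 = 0.92, approximation 82.2 % (t-test 81.9 %). The stated 86 % does not reproduce.
- Perceived quality at 150: 0.351 × √75 − 1.96 = 1.08, approximation 86.0 % (t-test 85.7 %). The stated 86 % reproduces here.

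The half-SD rule in the Table 2 footnote does not explain the 86 %. Half of 22.8 is 11.4, and that difference gives 98 to 99 %. The perceived-quality row thus matches the enrolled number, while the satisfaction row matches the effective number.

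**Step 2: further loss from 135 per arm (assumed).**

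| Analysed per arm | Share of 135 | Satisfaction | Perceived quality |
|---|---|---|---|
| 135 | 100 % | 98 % | 82 % |
| 128 | 95 % | 98 % | 80 % (79.9) |
| 118 | 87 % | 97 % | 77 % |
| 107 | 79 % | 95 % | 72 % |
| 95 | 70 % | 93 % | 67 % |

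**Step 3: slack.** By the normal approximation, 80 % power needs about 128 per arm for perceived quality and 63 for satisfaction. As shares of the 150 randomized these are 128/150 = 85 % and 63/150 = 42 %. Perceived quality tolerates almost no loss beyond the 10 % already allowed. Satisfaction tolerates a great deal.

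**Step 4: a rough check on early delivery.** If gestational age were normal with the Table 2 values, the share delivered before 36 weeks would be Φ((36 − 38.9)/2.5) = 12.3 % under usual care and Φ((36 − 40.2)/2.5) = 4.6 % under OB Nest. Applied to 135, that leaves about 118 and 129, with power of about 97 % for satisfaction and 78 % for perceived quality. Normality is not stated in the article, so this shows only an order of magnitude.

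**The case against.** The product 150 × 0.9 = 135 is correct, and a condensed article may leave survey completion to the full protocol. The 10 % is an upper limit and exclusions are expected to be minimal, so the unused part could absorb some survey loss. With no withdrawals or exclusions, the early-delivery model of step 4 leaves about 132 and 143, and perceived-quality power is 83 %. The article does not say whether a pregnancy loss counts as a withdrawal, nor that a woman delivered before 36 weeks goes unsurveyed. All this stands, and it is why the floor is described as not assured rather than as breached.

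A reader might infer that the gestational-age figures in Table 2 by themselves prove a loss above the whole 10 %. They do not. The 12 % needs a normal distribution that the article does not state, and it applies only to the usual-care mean; the OB Nest mean gives 4.6 %. The same normal model puts 11 % of usual-care deliveries and 24 % of OB Nest deliveries after 42 weeks, whereas the visit schedule in Table 3 ends its antenatal part at week 41. The model fits the tails poorly.

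A reader might also attribute the whole drop from 86 % to 77 % to missing surveys. About 4 of those 9 points come from using 150 instead of 135.

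None of these objections reaches the 86 % itself, which is wrong at the stated effective size even if every survey is returned.

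**Conclusion.** Two points hold. First, the 86 % power for perceived quality does not belong to the stated effective sample size: it is about 82 % at 135 per arm. This follows from the article's figures alone. Second, 135 per arm is not an assured floor for outcomes that depend on an e-mailed survey at 36 weeks, because the allowance as defined omits non-return and loss from follow-up by that time. How far the analysed number falls is unknown. Over an assumed 95 to 128 per arm, perceived-quality power is 67 to 80 %.

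The documents do not support the inference that the primary comparison is underpowered. Satisfaction keeps 93 % or more across this range and still has about 91 % at 87 per arm. For the primary outcome, bias from unreturned surveys may matter more than lost power.

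**What to change.** In Table 2, change the power for perceived quality to about 82 % at 135 per arm. In Sample size, state an expected completion for the survey outcomes separately from withdrawal and exclusion, and report power for satisfaction and perceived quality over a labelled range of analysed numbers, for example 95 to 135 per arm. Apply the same kind of completion allowance to the e-mailed stress survey at its own time points. Keep 135 per arm as the floor only for outcomes taken from the medical record.

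The cost is some wording and a few figures. No extra patients are needed. The only downside is a less favourable stated power for perceived quality.

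### Table 2's half-SD footnote does not fit the quality-of-care row (0.35 SD) or the visits row (0.64 SD fall), the 86 % power omits the 10 % attrition allowance, and the PIPC score behind it is not identified

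*Protocol article*

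**What the plan says.** **Sample size section and Table 2.** The quality row reads "Perceptions of quality of care 83.9 (SD 22.8) 91.9 86" % power: one control mean, one SD, one target and one power. The footnote states "All calculations 2-sided with alpha of 0.05" and "Continuous outcomes compared to a half of standard deviation increase".

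On numbers, the section says "We will enroll 300 patients in this study (150 patients per arm"). It adds "This accounts for a withdraw/post-randomization exclusion rate as high as 10" per cent, "so the effective sample size can be as low as 135 patients/arm".

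**Data collection, Quantitative.** Perceived quality is measured with the 30-item PIPC at 36 weeks, which has three subscales (communication, decision making, interpersonal style). The scoring rule is "Responses will be converted to a 0–100 scale for each subscale". No total is described and no subscale is singled out.

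**Analysis plan, Quantitative.** Each outcome is compared by t-test or chi-square test. "The comparison of outcomes will be considered significantly different between arms at a" P value below 0.05. The section does not say which PIPC score is the outcome.

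**Study purpose.** Perceived quality of prenatal care is part of the first research question, beside satisfaction, which is the primary outcome.

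**The concern.** The quality row disagrees with the text around it in three ways.

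1. **Effect size.** The footnote gives one rule for all continuous outcomes, and the row's own figures do not follow it. A reader who trusts the footnote would take the trial to have 86 % power for half an SD. The row in fact plans for a smaller effect.
2. **Sample size behind the power.** The section says attrition of up to 10 % is covered, so a reader expects the printed power to hold at 135 per arm. If the row was computed at 150, it overstates the power under the plan's own allowance.
3. **Variable.** The table plans one score and the scoring rule produces three. The power figure cannot be tied to a defined variable, and nothing in the article fixes in advance which score answers the quality part of the first research question.

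At stake is how a quality result will be read: what difference the trial was planned to detect, with what power, and on which score.

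**Working it through.** **Inputs**, all from the Sample size section and Table 2: two-sided alpha 0.05; 150 per arm enrolled; 150 × 0.90 = 135 per arm after attrition; and each row's control mean, SD and target.

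**Formula.** Power ≈ Φ( δ / (SD × √(2/n)) − 1.960 ), with n per arm. The opposite tail is negligible here.

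**Step 1: reproduce the 86 %.** δ = 91.9 − 83.9 = 8.0.
- n = 150: standard error 22.8 × √(2/150) = 2.633; 8.0/2.633 = 3.039; Φ(1.079) = 86.0 % (t-test: 85.7 %). This matches the printed figure.
- n = 135: standard error 22.8 × √(2/135) = 2.775; 8.0/2.775 = 2.883; Φ(0.923) = 82.2 % (t-test: 81.9 %). This does not match.

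Working backwards, 86 % power needs a difference of 8.00 points at 150 per arm and 8.44 points at 135 per arm. The row's 8.0 fits 150.

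**Step 2: compare with the primary row.** Satisfaction has δ = 115.6 − 108.4 = 7.2 and 7.2/14.4 = 0.500 SD. Power is 98.4 % at 135 per arm and 99.1 % at 150. The printed 98 % fits 135. The two rows therefore appear to rest on different sample sizes.

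**Step 3: check the footnote on every continuous row.**

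| Row | Difference / SD | In SD units |
|---|---|---|
| Satisfaction | 7.2 / 14.4 | 0.500 |
| Quality of care | 8.0 / 22.8 | 0.351 |
| Prenatal stress | 3.6 / 7.1 | 0.507 |
| Gestational age | 1.3 / 2.5 | 0.520 |
| Antenatal visits | −2.7 / 4.2 | −0.643 |

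Three rows agree with half an SD to within rounding of the targets. Quality is clearly smaller. Visits is larger and is a decrease.

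**Step 4: what the footnote would imply for quality.** 0.5 × 22.8 = 11.4 and 83.9 + 11.4 = 95.3. Power at 135 per arm: 11.4/2.775 = 4.108; Φ(2.148) = 98.4 %. At 150 per arm it is 99.1 %. Neither is 86 %.

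**Step 5: the score.** Table 2 has one quality mean and SD. The scoring rule gives three scores. The article prints no mean, SD or target for any subscale, so power for a subscale cannot be computed from it.

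**The case against.** The strongest reply is that nothing is miscalculated. Table 2 prints the row's mean, SD and target, so anyone can see that 8.0 points is being tested, and 86 % is right for those inputs at full enrolment. Even at 135 per arm the power stays above 80 %. The visits row has over 99.9 % power at either size. The outcome is secondary and did not set the sample size. All of this stands, and it limits the weight of the point. It does not remove the conflict between the footnote, the row and the attrition statement, which sit side by side in one section.

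A second reply is that this is a condensed article. How secondary scores are combined, and how multiplicity among them is handled, may be set out in an analysis plan that is not shown. This also stands, and it rules out a stronger reading. A reader might infer that three subscale tests at 0.05 are planned, giving up to 1 − 0.95³ = 14.3 % chance of a false positive, or 68–74 % power per subscale after a Bonferroni split. The article does not support this:
- It says each outcome is compared, and elsewhere treats perceived quality as one outcome.
- The 14.3 % assumes independent tests and counts errors in both directions.
- The 68–74 % assumes that every subscale has SD 22.8 and a gain of 8.0, and no such inputs are given.

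A reader might also assume that 83.9 is the average of the three subscales. Nothing says so. Nor does Table 2 reliably use the scaling in the Data collection section: its satisfaction mean of 108.4 cannot lie on the 0–100 scale defined there.

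**Conclusion.** The point holds as a set of internal contradictions about a secondary outcome.

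- The footnote is wrong for two of the five continuous rows: 0.35 SD for quality, and a 0.64 SD fall for visits.
- The quality row's 86 % holds at 150 per arm. At the 135 per arm that the section says is allowed for, it is about 82 %, a loss of about 4 percentage points.
- The row plans a single quality score that the scoring text does not identify.

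The figures rest on a two-sided 5 % comparison of two means with equal arms and the SD printed in Table 2. That the primary row was computed at 135 per arm is inferred from its rounded 98 %.

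A reader should not conclude that 86 % is an arithmetic error, that an inflated false-positive rate has been shown, or that the trial is too small. The sample size of 300 and the primary comparison are unaffected.

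**What to change.** 1. Correct the Table 2 footnote so that it no longer claims half an SD for every continuous row, and state the actual effects: 8.0 points (0.35 SD) for quality and −2.7 visits (−0.64 SD).
2. Restate the quality row's power as about 82 % at 135 per arm, and say that this is the size used.
3. Name the one PIPC score that 83.9 (SD 22.8) describes, make it the quality outcome before outcome data are examined by arm, and call the other PIPC scores supportive. If that score is a total, add a sentence to the Data collection section saying how it is formed. A new composite should not be created merely to fit the row.

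The cost is a few sentences and no new data. The downsides are a slightly less favourable power figure and supportive-only status for the remaining PIPC scores.
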